**Phase 1 and 2 Withdrawal of Participants**

Participants may voluntarily withdraw from participation at any time. The study staff may withdraw a participant one or more of the following reasons: failure to follow the instructions of the study staff; inability to complete the study requirements; or inability to reach participant by telephone after multiple attempts.

**Phase 1 and 2 Study Communication**

For any participant who indicates that they are willing to receive study communications via email, we will use Azure to send secure communications to them re: appointment scheduling, missed appointments, etc. Content from the study’s IRB-approved letters will be included in the emails. Participants will also be provided with a dedicated study phone number to call with any questions or concerns.

**Phase 1 and 2 Data Collected at Duke**

All study data that are collected at Duke, including MRI results, will be transferred to a VA secured server (see storage locations listed below) using a VA-owned encrypted thumb drive.

**Data Analysis and Statistical Considerations**

**Phase 1:** Based on requirements of the CDA-1 that a controlled intervention trial is not allowed, feasibility is the primary focus of the proposed study. Without a control group, neither a power analysis nor effect size calculation are indicated. However, primary endpoints have been operationalized to allow for quantitative assessment. Specifically, we will determine if we meet successful recruitment as enrolling 18 subjects, retention as 14 subjects completing 90% of study procedures (which corresponds to ~20% attrition rate), and acceptability as  7/10 on 10-point satisfaction scale.

We will conduct an exploratory analysis of the secondary outcome data in order for the candidate to gain experience with analysis of neuroimaging and psychometric data, to prepare for a pilot efficacy trial in the CDA-2, and for descriptive purposes for the CDA-2 application. Given the small number of subjects and large number of variables, we will focus on the correlation between changes on RSFC pre- and post-rTMS and change in the number of cigarettes smoked in the past 24 hours, since we do not expect a change in psychiatric symptoms. We will calculate confidence intervals around the effect size to gain an idea of the variability in the subsequent trial.

**Phase 2:** Feasibility endpoints have been operationalized to allow for quantitative assessment. Specifically, we will determine if we meet successful recruitment by enrolling 50 subjects and retention with 40 subjects completing 90% of study procedures (which corresponds to a 20% attrition rate). We will determine if Veterans find the intervention acceptable based an average score of  7/10 on a 10-point satisfaction scale.

Primary smoking outcome will be 7-day point prevalence abstinence based on subject self-report and confirmed using exhaled CO level at each follow-up assessment (i.e., end-of-treatment, 3-months post-quit date), with abstinence rates averaged over all assessments to take advantage of all available data and adjust for within-subjects clustering of data.115 This definition of abstinence is consistent with those previously used in studies of smoking cessation in Veterans.28 Non-abstinence will be defined as self-reported smoking (or other tobacco use) for 7 consecutive days or at least once a week for 2 consecutive weeks. Secondary outcomes will include daily number of cigarettes smoked, subjective levels of withdrawal, craving, and urges to smoke, 7-day point prevalence at 3-months post-quit date, as well as smoking relapse, defined as smoking 5 or more cigarettes per day for 3 consecutive days. We will evaluate 7-day point prevalence smoking abstinence by calculating a dichotomous outcome variable (abstinent or not abstinent) to determine the proportion of participants with bioverified abstinence at each assessment from quit date through 3 months follow-up. Due to the relatively small sample size, we will describe the rates of smoking abstinence by calculating the proportion of participants who are confirmed to be abstinent. We will calculate confidence intervals around the effect size to determine the level of variability expected in the subsequent full RCT.

Participants will be considered abstinent if they meet certain criteria, which we have used in prior work.97 For participants taking NRT at the time of follow-up, they will be considered abstinent if they self-report prolonged abstinence and provide a CO reading < 5 ppm. For those not taking NRT, abstinence will be based on: a) self-reported prolonged abstinence, b) absence of any biochemical samples indicating smoking (CO ≥ 5 ppm or cotinine ≥ 6 ng/mL), and c) presence of at least one biochemical sample indicating abstinence (CO < 5 ppm and/or cotinine < 6 ng/mL).

Comparisons of continuous demographic and clinical data will be completed with linear regressions. Comparisons of dichotomous demographic and clinical data will use generalized linear models using a binomial distribution. Regarding 7-day point prevalence smoking abstinence outcomes at end-of-treatment, and 3-months; odds ratios and 95% confidence intervals will be computed from estimates obtained in generalized linear models. A longitudinal analysis using generalized linear models will also be conducted on abstinence across end-of-treatment, and 3-month time periods with predictors of treatment arm, time in months (standardized and centered), and the treatment arm-by-time interaction. All missing smoking data will be imputed as non-abstinent. All analyses will be conducted in R version 4.0.4.116

We will also complete analysis of neuroimaging data to determine target engagement. Specifically, we will focus on the correlation between changes on rsFC pre- and post-rTMS and change in the number of cigarettes smoked in the past 24 hours. We will also use a data-driven approach by employing group independent component analysis (ICA) to compare functional network connectivity (FNC) between active- and sham-rTMS groups including FC between rTMS target and right posterior insula.117

For the neuroimaging data, movement and scan artifacts will be detected using Artifact Detection Tools118 and included in the rsFC analyses as covariates of no interest. Group-level analyses will be conducted in SPM12. rsFC analyses will be confined to a bilateral insula regional of interest (ROI) mask defined from the Automated Anatomical Labeling (AAL) atlas with a significance threshold of p < .001 uncorrected, cluster extent > 10 voxels. Exploratory whole brain analyses will also be conducted with a significance threshold of p < .001 uncorrected, cluster extent > 50 voxels.

In the event that software required for analysis are not available through VINCI, deidentified data will be moved to Duke University Medical Center for analysis. Data will be emailed.

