The desire to quit smoking among Veterans is not lacking. Approximately 60-70% of all Veterans who smoke tobacco express interest in smoking cessation (Miller et al, 2001). A strong dose-response relationship between treatment intensity and cessation rates does exist (Fiore et., 2000). The most efficacious strategies found in VA smoking cessation clinics combine multiple formats of cognitive-behavioral interventions, including self-help materials, group therapy, and telephone counseling, resulting in a 23% abstinence rate (Fiore et al, 2000). These rates worsen in the context of comorbid psychiatric conditions, with specialty-based care smoking cessation efforts negatively affected by limited access and poor adherence (Jonk et al, 2005). Clinic attendance rates at specialty smoking cessation clinics are approximately 13-14% for all Veterans, and those with PTSD even less likely to follow up (McFall et al, 2010). Unfortunately, among Veterans with PTSD who do present to smoking cessation clinics, the efficacy of interventions is lower (McFall et al, 2010). This was demonstrated in the largest smoking cessation trial in Veterans with PTSD, with a biochemically verified (bio-verified; exhaled CO < 8 ppm or urine cotinine < 100ng/mL) cessation rate of only 4.5% at 12-months (McFall et al, 2010). These statistics underscore the urgency to consider alternative interventions for smoking cessation in this clinical population, including neuromodulaiton modalities such as rTMS.

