Overall Design: Fifty eligible participants will be randomized to one of 2 conditions: active-rTMS + CBT + NRT (n=25) or sham-rTMS + CBT + NRT (n=25). The full randomization sequence will be generated *a priori*. Participants will receive a baseline MRI scan, 5 daily neuronavigated active or sham rTMS treatments the week prior to their quit date, followed by a post-treatment MRI scan. In order to be able to use the fMRI results to inform placement of the TMS coils, there may be up to a two-week lag between the first MRI and the first TMS treatment session. All participants will receive 5 sessions of CBT for smoking cessation in which session 3 is designated as the quit date. All participants will also receive prescriptions of nicotine replacement in the form of 21 mg, 14 mg, and/or 7 mg patches and 2-4 mg nicotine gum or lozenges starting on the quit date and continuing for up to 90 days at individually tapered doses. All rTMS and MRI procedures will occur at Duke University Medical Center (DUMC). Participants will sign a Duke consent form and HIPAA authorization for those procedures.

We hypothesize that neuronavigated rTMS combined with CBT and NRT will be a safe, feasible, and effective method for smoking cessation in our study population. We anticipate being able to effectively recruit and retain eligible subjects in the study. Our primary feasibility endpoint will help determine successful completion of the study intervention and justification to continue this line of research. Recruitment will target enrolling 50 subjects, with a goal of 40 or more subjects completing at least 90% of all study procedures (>80% retention rate). We hypothesize that active- as compared to sham-rTMS will result in greater 7-day point prevalence abstinence rates (biochemically verified by exhaled carbon monoxide < 5 ppm) at end-of-treatment, and 3-month follow-up time points. We also hypothesize that active-rTMS will result in an increase in functional connectivity between the cortical rTMS target and the insula, therefore demonstrating target engagement. We also anticipate network-level differences in rsFC between active- vs sham-rTMS groups. We will also monitor levels of nicotine dependence, cravings, withdrawal, prolonged abstinence, psychiatric symptoms related to PTSD and depression, and alcohol use.

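### The primary smoking outcome is defined by CO alone but scored by a test that changes with NRT use at follow-up, with no NRT-free interval before cotinine counts against a participant

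*Protocol*

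**What the plan says.** **Headline definition.** The Phase 2 part of Data Analysis and Statistical Considerations defines the primary smoking outcome as self-reported 7-day point prevalence abstinence, "confirmed using exhaled CO level at each follow-up assessment (i.e., end-of-treatment, 3-months post-quit date", "with abstinence rates averaged over all assessments". The hypothesis in the Phase 2 Overall Design paragraphs agrees: 7-day abstinence, "biochemically verified by exhaled carbon monoxide < 5 ppm". Those paragraphs list prolonged abstinence separately, among the further measures to be monitored.

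**Working criteria.** The next paragraph of the analysis section says who counts as abstinent.
- On NRT: "For participants taking NRT at the time of follow-up, they will be considered abstinent if they self-report prolonged abstinence and provide a CO reading" below 5 ppm.
- Not on NRT: self-reported prolonged abstinence, "absence of any biochemical samples indicating smoking (CO ≥ 5 ppm or cotinine ≥ 6 ng/mL", and "presence of at least one biochemical sample indicating abstinence (CO < 5 ppm and/or cotinine < 6 ng/mL".

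**Cotinine collection.** Phase 2 Study Procedures (Biochemical Verification of Abstinence) has urine cotinine taken post-treatment and at 3 months, from participants who no longer use NRT. Table 2 marks it at 3 months only.

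**NRT period.** In the Phase 2 Overall Design, NRT starts on the quit date, "continuing for up to 90 days at individually tapered doses". Additional Study Interventions has it offered for at least 60 days. The joint Study Interventions section has it prescribed at medical screening and continued as needed during the study.

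**Other cut-off in the document.** The background reports that an earlier cessation trial in Veterans with PTSD used "exhaled CO < 8 ppm or urine cotinine < 100ng/mL".

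**Analysis.** Odds ratios are estimated at each visit. A longitudinal model has arm, time and arm-by-time terms. Missing smoking data count as non-abstinent.

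**The concern.** One endpoint has two definitions. A reader of the hypothesis and the headline expects a 7-day, CO-confirmed outcome. The data would be scored on prolonged abstinence, with a further biochemical failure rule for some participants.

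Which test applies depends on NRT use at the visit, which is settled after randomisation and can change over time. If the share on NRT differs between end-of-treatment and 3 months, the visits are scored with different mixtures of tests. The outcome averages those visits, and the model estimates a time trend across them.

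The working criteria also treat a participant as not taking NRT from the moment NRT stops. Restricting cotinine to non-users concedes that NRT itself produces cotinine, yet no interval is required between the last NRT use and the sample. A true quitter who finishes a course just before the 3-month visit can therefore be scored as a smoker.

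The effect size and its confidence interval from this pilot are meant to inform a full randomised trial, so an unclear endpoint would carry forward.

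**Working it through.** The protocol gives no power or expected rate for abstinence in this trial, so there is no stated figure to reproduce. The check compares the rules and timing, then sizes the effect under assumptions.

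**1. The rules side by side**

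| | Headline and hypothesis | On NRT | Not on NRT |
| --- | --- | --- | --- |
| Self-report | 7-day | prolonged | prolonged |
| CO below 5 ppm | required | required | required unless a cotinine sample confirms |
| Cotinine 6 ng/mL or more | not mentioned | not tested | fails |
| NRT-free interval | not applicable | not applicable | none stated |

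**2. Timing.** The quit date is session 3 of 5 weekly sessions. If end-of-treatment is session 5 (an assumption; Phase 2 does not date the visit), it falls (5 − 3) × 7 = 14 days after the quit date, well inside a 60- to 90-day NRT period. Three months is about 3 × 30.4 = 91 days, just past the 90-day limit. On that reading most participants are on NRT at the first visit and the group is mixed at the second.

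**3. Effect of rejecting true quitters.** Let t be true abstinence, q the share on NRT at the visit, and r the share of true quitters off NRT whom the cotinine rule rejects.

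Observed rate = t × [q + (1 − q)(1 − r)]

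Assumed inputs: t = 30% in both arms at both visits; q = 100% at end-of-treatment; r = 15% to 50%. End-of-treatment then reads 30%. At 3 months:

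| Share on NRT | r = 15% | r = 50% |
| --- | --- | --- |
| Active, q = 40% | 0.30 × 0.91 = 27.3% | 0.30 × 0.70 = 21.0% |
| Sham, q = 60% | 0.30 × 0.94 = 28.2% | 0.30 × 0.80 = 24.0% |
| Both arms, q = 50% | 0.30 × 0.925 = 27.75% | 0.30 × 0.75 = 22.5% |

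- Apparent fall with no relapse: from 30 − 28.2 = 1.8 points to 30 − 21.0 = 9.0 points. With q = 50% in both arms it is still 2.25 to 7.5 points.
- Arm difference with no treatment effect: 28.2 − 27.3 = 0.9 points to 24.0 − 21.0 = 3.0 points. With equal q it is 0. In an arm of 25 that is 0.2 to 0.75 of a participant.

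**4. Effect of detecting false reporters unequally.** Let f be the share falsely reporting abstinence, s1 the detection by CO alone, and s2 the detection by CO or cotinine.

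Arm difference = f × (difference in q) × (s2 − s1)

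Assumed inputs: f = 10% to 20%; s1 = 60% to 80%; s2 = 95%.
- NRT use 30% against 60%: 0.10 × 0.30 × 0.15 = 0.45 points to 0.20 × 0.30 × 0.35 = 2.1 points.
- NRT use 20% against 80%: 0.10 × 0.60 × 0.15 = 0.9 points to 0.20 × 0.60 × 0.35 = 4.2 points, about one participant in 25.

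Here cotinine is correctly catching smokers; the fault is only that it does so in part of the sample. Under both mechanisms the arm with less NRT use looks worse.

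**5. Cut-offs.** 100 / 6 = 16.7. The sample is urine, but the 6 ng/mL rule names no specimen.

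**The case against.** The case on the other side is substantial.

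- **The split is deliberate.** Cotinine cannot separate smoking from NRT in someone using NRT, and the procedures section restricts it accordingly. The protocol says the criteria come from prior work. This stands: testing NRT users by CO only is not an oversight. It does not explain the missing NRT-free interval or the mismatch with the headline definition.
- **The off-NRT rule is not uniformly harder.** A reader might infer that people off NRT always face the stricter test. The third off-NRT criterion accepts one confirming sample of either kind, so a participant with no cotinine sample passes on CO alone, and one with no CO reading can pass on cotinine. An NRT user must supply CO. This stands, and the calculation in step 3 leaves it out.
- **The cut-offs do not contradict each other.** A reader might infer that 6 ng/mL conflicts with 100 ng/mL. The larger figure describes an earlier trial, which also used a different CO limit. The documents do not show which value suits urine here.
- **The sizes are assumed.** Nothing in the protocol indicates that active rTMS changes NRT use. The differences are small beside sampling error: at 30% in both arms of 25, the 95% interval for a difference is about ±1.96 × √(2 × 0.3 × 0.7 / 25) = ±25 points. Recruitment and retention are the Phase 2 feasibility endpoints, and abstinence serves to estimate an effect size.
- **The CO-only hypothesis may be shorthand.** The procedures section adds cotinine to CO. That is possible for the hypothesis, but the analysis section also states a CO-only definition immediately before departing from it.

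**Conclusion.** The point holds as an inconsistency in the primary smoking outcome together with a rule that can misclassify quitters. The headline and the hypothesis say 7-day abstinence confirmed by CO; the working criteria say prolonged abstinence, plus a cotinine failure rule for those off NRT. The procedures text and Table 2 disagree on whether cotinine is collected post-treatment. Those statements are in the protocol and need no assumption.

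The main consequence is for the averaged outcome and the time terms, where a change of test can pass for relapse: about 2 to 9 points at 3 months under the inputs in step 3, and present even when the arms use NRT equally. This rests on end-of-treatment falling about 14 days after the quit date, on all participants being on NRT then, and on the assumed rejection rates.

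A reader might go further and conclude that the comparison is biased against active rTMS. The documents do not support that. Such a bias requires unequal NRT use, its direction depends on which arm uses less, and it is about 1 to 3 points in step 3, less than one participant per arm. Nor do they show that 6 ng/mL is the wrong cut-off: it is unexplained and lacks a specimen. The change is worth making because it is cheap and the pilot's estimates feed a later trial.

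**What to change.** 1. Use one primary verification for every participant at both visits: self-reported 7-day abstinence plus CO below 5 ppm, as the headline definition and the hypothesis already say. Keep prolonged abstinence as a separate outcome with its own definition.
2. Report the cotinine-augmented definition as a sensitivity analysis, limited to participants who have been off NRT for a minimum number of days stated in advance. Record the date of last NRT use to support this.
3. State the cotinine cut-off for urine, with its justification and a traceable source.
4. Reconcile the cotinine visits in Phase 2 Study Procedures with Table 2, and the descriptions of the NRT period with one another, since both determine who can be tested and when.

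The cost is wording and one recorded date; no new samples are needed. The downside is that CO detects only recent smoking. The cotinine analysis addresses this only for participants off NRT, so undetected smoking among NRT users remains a stated limitation, as it is under the present rule.

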While the ideal brain stimulation target is unknown, rTMS applied over the superior frontal gyrus (SFG) demonstrated differential effects on cravings, depending on the cue presented: high-frequency 10-Hz TMS applied to SFG increased cravings to smoking cues, yet decreased cravings to neutral cues (Rose et al, 2011). In another study, 20-Hz rTMS was applied sequentially over the left DLPFC and the medial SFG over 10 days, which resulted in a significant reduction in nicotine cravings as well as resting brain activity as measured by the functional magnetic resonance imaging (fMRI) measures, cerebral blood flow and brain entropy (Chang et al, 2018). In the largest published trial (n=115), rTMS was applied to lateral prefrontal cortex and insula bilaterally using a BrainsWay H4 deep TMS (dTMS) coil following presentation of smoking cues over 13 sessions in a population of heavy smokers with failed previous treatments, high- and low-frequency stimulation resulted in significantly reduced cigarette consumption with an abstinence rate of 44% at the end of treatment and an estimated 33% at 6-month follow-up (Dinur-Klein et al, 2014). This work led to an unpublished multicenter RCT using the H4 dTMS coil in chronic, heavy smokers (n=262 enrolled, n=168 completers), which demonstrated after 3 weeks of treatments plus 3 weeks of follow-up a 28.4% continuous quit rate in the active group compared to 11.7% in the sham group (p=0.0063). Based on this study, the FDA granted 510(k) clearance in August 2020 for dTMS as an aid in short-term smoking cessation in adults (Globe Newswire, 2020). Despite this exciting and important development, this trial excluded patients with recent psychiatric illness and those using NRT, smoking cessation drugs or behavioral therapy (National Library of Medicine, NLM). The currently proposed study will help fill this gap by assessing rTMS as a smoking cessation treatment in a special population that was excluded from prior trials (Veterans with PTSD) while offering NRT and psychotherapy.

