**Phase 2 Selection of Subjects**

We estimate that approximately 120 Veterans will be consented and screened, with 50 being enrolled and randomized to a study condition, and a final sample of 40 participants who complete all study procedures. However, given that the subsequent full RCT will use intent-to-treat analysis, we will include all 50 participants in descriptive statistics and primary analyses. Study inclusion and exclusion criteria are outlined below.

Phase 2 Inclusion/Exclusion Criteria:

| Subjects must meet **all** inclusion criteria: | Subjects must not have **any** exclusion criteria: |
| --- | --- |

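### With 25 per arm and possibly low quit rates, an ordinary GLM odds ratio for abstinence has no finite value if an arm has no abstainers; pre-specifying a penalised estimate and a risk difference is a cheap safeguard

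*Protocol*

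**What the plan says.** Phase 2 randomises 50 participants to "active-rTMS + CBT + NRT (n=25) or sham-rTMS + CBT + NRT (n=25") (Phase 2 Research Design and Methods, Overall Design). On the analysis set, Phase 2 Selection of Subjects says that "we will include all 50 participants in descriptive statistics and primary analyses".

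The Phase 2 part of Data Analysis and Statistical Considerations makes these choices for 7-day point prevalence abstinence:

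- At end-of-treatment and 3 months, "odds ratios and 95% confidence intervals will be computed from estimates obtained in generalized linear models".
- A longitudinal generalized linear model has "predictors of treatment arm, time in months (standardized and centered), and the treatment arm-by-time interaction".
- "All missing smoking data will be imputed as non-abstinent".
- Abstinence proportions are also described, because the sample is small.
- The purpose of the interval is given: "We will calculate confidence intervals around the effect size to determine the level of variability expected in the subsequent full RCT".

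No test, significance level or interval type is named for abstinence, and nothing is said about sparse data. Recruitment and retention are the primary feasibility outcome. Abstinence belongs to a separate efficacy aim, which is to estimate an effect size.

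**The concern.** A binomial model fitted by maximum likelihood has no finite log-odds ratio when one of the two groups has no events. Software stops at an arbitrary large coefficient with a far larger standard error. The background section makes an empty sham arm conceivable. It reports a bio-verified "cessation rate of only 4.5% at 12-months" in the largest smoking cessation trial in Veterans with PTSD, and a "28.4% continuous quit rate in the active group compared to 11.7% in the sham group" in the multicentre deep-TMS trial. Scoring missing data as smoking pushes observed rates down further.

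At stake is the one product the efficacy aim is meant to deliver: a between-arm effect size with an interval that the full RCT can be planned on. The arm-by-time model has four arm-by-visit cells, and one empty cell is enough to make its coefficients diverge.

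**Working it through.** **The plan's own figure.** 40 completers / 0.80 = 50 enrolled, so the stated 20% attrition reproduces. No power or detectable difference is stated for abstinence, so there is none to reproduce.

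**Inputs.** n = 25 per arm (Overall Design); sham rates of 4.5%, 11.7% and 23% and an active rate of 28.4% (Background and Significance). The 23% is the abstinence rate quoted for the best multi-format care in VA clinics. The 8% is an assumed value between the first two.

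**Step 1: chance of no sham abstainers at one visit**, (1 − p)^25:

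| Sham rate | Chance of 0/25 |
|---|---|
| 4.5% | 0.955^25 = 31.6% |
| 8% (assumed) | 0.92^25 = 12.4% |
| 11.7% | 0.883^25 = 4.5% |
| 23% | 0.77^25 = 0.15% |

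Suppose the 20% attrition is scored as smoking on top of these rates (an assumption, since the cited rates may already include it). Then 4.5% becomes 3.6% and 11.7% becomes 9.4%, and the chances rise to 40.0% and 8.6%.

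**Step 2: two visits.** The chance that at least one sham visit is empty lies between full correlation and independence of visits. At 4.5% it is 31.6% to 1 − (1 − 0.316)² = 53%. At 11.7% it is 4.5% to 8.7%. This is the exposure of the arm-by-time model. For abstinence averaged over both visits, every sham participant must be non-abstinent at both: 0.316² = 10% to 32% at 4.5%, and 0.2% to 4.5% at 11.7%.

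**Step 3: what the stated estimator returns for 7/25 against 0/25.** A binomial `glm()` in R (4.3.3 here; the protocol names 4.0.4) gives a log-odds ratio of 18.6 (odds ratio about 1.2 × 10^8) with standard error 2151. The Wald 95% interval is 0 to infinity. The default `confint()` gives 1 × 10^−78 to NA. On the same table Fisher's exact p is 0.0096, the likelihood-ratio p is 0.0010, and a correctly solved profile-likelihood lower limit is 4.07, with no finite upper limit.

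**Step 4: the alternatives on the same table.**

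- For a two-group comparison, Firth's odds ratio equals the odds ratio after adding 0.5 to each cell: (7.5 × 25.5)/(18.5 × 0.5) = 20.7. It is finite, though its interval will be wide, as it should be.
- Newcombe risk difference: the Wilson limits are 0.143 to 0.476 for 7/25 and 0 to 0.133 for 0/25. The lower limit is 0.28 − √[(0.28 − 0.143)² + 0.133²] = 0.09. The upper limit is 0.28 + (0.476 − 0.28) = 0.48.

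**Step 5: illustrative chance that a 95% interval excludes no effect.** All 26 × 26 outcomes were enumerated, and a zero cell was counted as non-exclusion for Wald:

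| Active vs sham | Wald | Firth | Newcombe |
|---|---|---|---|
| 28.4% vs 11.7% | 24% | 30% | 33% |
| 28.4% vs 8% | 31% | 48% | 49% |
| 28.4% vs 4.5% | 32% | 68% | 67% |

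With both arms at 4.5%, 8% and 11.7%, false exclusion is 1.6%, 4.1% and 5.2% for Firth, 0.3%, 1.8% and 3.7% for Newcombe, and 0.0%, 0.2% and 0.9% for Wald. The alternatives therefore do not gain by inflating error.

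**The case against.** Two stronger readings are tempting, and the document supports neither.

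A reader might infer that the plan would declare a strong effect non-significant, since the default Wald p for 7/25 against 0/25 is 0.993. But the protocol states no null hypothesis test, p-value or significance level for abstinence, and the Wald interval is only one reading of its wording. The likelihood-ratio test from the same model gives p = 0.0010. The planned visit-level proportions would show 28% against 0% to any reader.

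A reader might also infer a loss of some 35 percentage points in power from the last row of the Step 5 table. That row pairs a 12-month rate in Veterans with PTSD with an active rate from a civilian trial that excluded recent psychiatric illness, NRT and behavioural therapy. Here both arms receive CBT and NRT, and the outcomes are measured earlier. The only pair from a single trial is 28.4% against 11.7%, where the difference is 7 to 9 points. Outside empty cells the Wald interval costs little: against Newcombe, 5 to 7 points at the three sham rates.

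It can also be said that interval type and zero-cell handling belong in an SAP, which is not shown. That carries weight for the interval type. It does not dispose of the point, because the protocol itself fixes the estimator. With an empty arm, no interval method gives the ordinary maximum-likelihood odds ratio a finite estimate or upper limit.

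**Conclusion.** The point holds as a low-cost improvement. With an empty arm at a visit, the planned odds ratio and its upper limit are not finite, and a Wald interval carries no information, so the effect size and interval intended for the full RCT could not be reported in that form. The risk per visit is about 1 in 22 at the cited sham rate and about 1 in 3 only if sham abstinence is as low as 4.5%. It is negligible near 23%. These figures assume independent participants and a common rate within the arm. The interval comparisons further assume a Wald interval and are illustrative only; losses beyond 7 to 9 points need a sham rate well below 11.7%. The raw abstinence data and the primary feasibility outcome are unaffected.

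**What to change.** In the Phase 2 text of Data Analysis and Statistical Considerations:

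- For abstinence at end-of-treatment and at 3 months, estimate the odds ratio by Firth penalised-likelihood logistic regression with penalised profile-likelihood 95% intervals.
- Use bias-reduced estimation in the longitudinal arm-by-time model too.
- Report alongside these the risk difference with a Newcombe (or Miettinen-Nurminen) 95% interval, which remains defined with an empty arm and can be carried directly into planning.

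This should be written before outcome data are seen, because choosing a rescue method after an empty cell appears would be post hoc. If an SAP already specifies such a method, a cross-reference is enough.

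The cost is a few sentences and standard R packages, with no new data or participants. The downside is slight shrinkage of the odds ratio toward 1 and small differences from ordinary GLM output when events are plentiful.
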